#### **Exploring carers' experience in the iSupport program:**

PhD student, [name] will analyse the qualitative data collected from online carer support groups meetings and downloaded text messages between participants and facilitators. She will be supervised by PI [name] in data analyses. Audio-recorded meetings data will be transcribed verbatim for analysis using NVivo Transcription software. Transcripts will be entered into a computer-assisted qualitative data analysis program, NVivo13, for data management to facilitate coding. Thematic analysis through coding, grouping codes and summarising codes into themes will be applied (Nowell, Norris, White, & Moules, 2017). Findings will be discussed in regular team meetings to reach consensus.

#### **Measuring the cost-effectiveness of the iSupport program:**

The cost effectiveness analysis will be undertaken by [name] and will be supervised by CI [name]. The primary outcome will be the incremental cost per quality adjusted life years (QALYs) gained for the intervention compared to usual care. Resources associated with the development and implementation of the intervention will be documented and costed according to established best practice guidelines (Drummond, Sculpher, Claxton, Stoddart, & Torrance, 2015). The primary measure of effectiveness will be the incremental gains in

QALYs from the perspective of carers and people with dementia. SF-12 responses between baseline and 6 months will be converted into health state utilities for the calculation of QALYs for carers using the SF-6D preference based scoring algorithm developed by Brazier and colleagues (Brazier et al., 2017). DEMQOL-Proxy responses will be similarly converted using the preference-based scoring algorithm developed by Mulhern and colleagues (Mulhern et al., 2013). Data on health and social care service use for carers and care recipients will be collected via interview from the carers using the RUD monthly. Pre-baseline resource use data will provide additional baseline variables to control for potential confounding. The difference between pre- and post-baseline use of health services will be used to measure changes in carers' and care recipients' levels of utilisation and cost of health services for participants in both study arms.

Unit costs will be derived from following guidelines for conducting economic evaluations in Australia from published sources provided by Medicare, hospital finance departments and Australian Refined Diagnosis Related Groups cost weights. Cost of nursing home care will be calculated using basic daily and accommodation fees apportioned according to length of stay. An assessment of the sensitivity of the results obtained to variation in measured resources, effectiveness and/or unit costs will be undertaken using appropriate one-way and multi-way sensitivity analysis. A budget impact analysis will also be conducted, extrapolating the within trial assessment of costs and outcomes to a population level.

**Data linkage** –what linkages are planned or anticipated?

Medicare Benefits Schedule (MBS) and/or Pharmaceutical Benefits Scheme (PBS) data of carers and care recipients will be extracted to collect information on health services utilisation. MBS and PBS consent form provided by Services Australia (see Appendix E) will be used with the participants to gain consent to allow Services Australia to release MBS and PBS data. The data provided by Services Australia will be linked to other data collected by online survey, self-report with the participants (for example information responses to surveys about their health and quality of life and basic demographic information (for example age, gender) and caregiver status as well as use of other health and social care resources collected via the RUD questionnaire. This will enable the cost-effectiveness analysis for the project to occur.

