### **Methodological approach**

#### ***Study Design***

A multicentre RCT with carers of PLWD will be conducted to test the primary and secondary hypotheses. The intervention will last 12 months. The cost effectiveness analysis will be undertaken alongside the RCT. A qualitative descriptive design will be applied to explore carers' experience in the program using data from the virtual carer support group meetings. The across-method triangulation used in the study via a combination of an RCT and a qualitative strand will facilitate a more holistic understanding of iSupport implementation (Denzin, 2017).

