#### **Primary measures:**

- (1) Carers: SF-12 (Ware, Kosinski, & Keller, 1996): The SF-12 includes 12 items measuring two domains: mental health-related QoL and physical health-related QoL. Construct validity is 0.92 for the mental component and 0.91 for the physical component. The test-retest reliability for the mental component is 0.76 and for the physical component is 0.89. Higher scores indicate better QoL.
- (2) Care recipients' Quality of Life in Alzheimer's Disease (QOL-AD)-Proxy (Logsdon, Gibbons, McCurry, & Teri, 2002): This scale has 13 items. It has an internal consistency of 0.84-0.86 and test-retest reliability of 0.76-0.92. Higher scores indicate better QoL.

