#### **Measures for cost-effectiveness:**

- (1) The primary measure of cost-effectiveness will be the incremental gains in QALYs from the perspective of carers and people with dementia compared to usual care.

Resources associated with the development and implementation of the intervention will be documented and costed according to established best practice guidelines (Drummond et al., 2015). SF-12 responses between baseline and 12 months will be converted into health state utilities for the calculation of QALYs for carers using the SF-6D preference-based scoring algorithm developed by Brazier et al. (Brazier, [name], Salomon J, & Tsuchiya, 2017). QOL-AD-Proxy responses will be similarly converted using the preference-based scoring algorithm developed by Comans et al. (Comans et al., 2020).

- (2) Linked administrative health data from Data Linkage Services, including Pharmaceutical Benefits Scheme (PBS) and Medicare Benefits Schedule (MBS) utilisation, and hospital and emergency department uses, will be used to capture health service use for PLWD and their carers for 12 months prior and 12 months post recruitment with permission of the carers and their care recipients (when appropriate). Pre-baseline resource use data will provide additional baseline variables to control for potential confounding. The difference between pre- and post-baseline use of health services will be used to measure changes in PLWD's levels of utilisation and cost of health services in both study arms.
- (3) Data on health and social care visits outside those provided by MBS will be collected from participants using the resource utilisation in dementia (RUD) questionnaire (Wimo, Wetterholm, Mastey, & Winblad, 1998).
- (4) Unit costs will be derived from hospital finance departments and Australian Refined Diagnosis Related Groups cost weights. Cost of nursing home care will be calculated using basic daily and accommodation fees apportioned according to length of stay.

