**Participant follow up – how are participants monitored during the study?**

All carers in this study will undertake an online survey at three time points: baseline, 6 months and 12 months. The survey will enable researchers to monitor the effectiveness and cost-effectiveness of the education intervention for carers. Carers will also undertake a monthly 10-minute survey (online or hardcopy) to document the previous month health care services utilisation. Carers in the intervention group will also participate in monthly online carer group meeting for 12 months. The meetings will enable researchers to monitor how carers in the intervention group share their learning experience with peers and support each other.

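### The cost-effectiveness analysis section contradicts the measures section on the carer QALY window (6 against 12 months) and on the care-recipient utility instrument (DEMQOL-Proxy against QOL-AD-Proxy)

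*Protocol*

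**What the plan says.** The Protocol describes the QALY calculation twice.

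- Under *Measures for cost-effectiveness*: "SF-12 responses between baseline and 12 months will be converted into health state utilities for the calculation of QALYs for carers". For the person with dementia: "QOL-AD-Proxy responses will be similarly converted using the preference-based scoring algorithm", citing one published value set.
- Under *Measuring the cost-effectiveness of the iSupport program*, which instructs the analyst: "SF-12 responses between baseline and 6 months will be converted into health state utilities for the calculation of QALYs for carers". For the person with dementia: "DEMQOL-Proxy responses will be similarly converted using the preference-based scoring algorithm", citing a different published value set.

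The analysis section and Objective 2 both make incremental cost per QALY the primary outcome of the economic evaluation. It serves Aim 2 and the third secondary hypothesis.

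The care-recipient quality-of-life instrument under *Primary measures* is "Care recipients' Quality of Life in Alzheimer's Disease (QOL-AD)-Proxy". On timing, *Study Design* states "The intervention will last 12 months", and *Participant follow up* states "All carers in this study will undertake an online survey at three time points: baseline, 6 months and 12 months". Linked administrative data are to "capture health service use for PLWD and their carers for 12 months prior and 12 months post recruitment".

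**The concern.** An economist cannot follow both sections. They differ on how long carer QALYs accrue, and on which questionnaire and value set supply the care-recipient utilities. Neither section is said to prevail. The outlier is the section that tells the analyst what to compute.

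Three things are at stake:

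- **Mismatched windows.** If QALYs come from the analysis section and costs from the measures section, 6 months of carer benefit is set against 12 months of cost.
- **A care-recipient utility that does not fit the listed data.** An algorithm built for DEMQOL-Proxy cannot score QOL-AD-Proxy responses, because they are different questionnaires.
- **An open choice.** With two windows and two instruments in the protocol, the headline economic result could be settled after the data are seen, and either choice could be defended from the text.

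**Working it through.** There is no stated figure to reproduce, because the protocol reports no utilities, expected QALY gain or expected cost-effectiveness ratio. The check is mainly a comparison of the text.

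**Step 1. The two sections side by side**

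| Item | Measures section | Analysis section | Rest of the protocol |
|---|---|---|---|
| Carer QALY window | 0 to 12 months | 0 to 6 months | 12-month intervention; surveys at 0, 6 and 12 months; primary hypotheses at 12 months |
| Care-recipient instrument | QOL-AD-Proxy | DEMQOL-Proxy | QOL-AD-Proxy is a primary measure and is named in the primary hypotheses |
| Value set | the one cited for QOL-AD-Proxy | the one cited for DEMQOL-Proxy | both appear in the reference list |
| Period for service use | linked data for 12 months after recruitment | none stated (monthly questionnaire only) | no shorter period given |

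DEMQOL-Proxy is absent from the primary, secondary and cost-effectiveness measures. Outside the analysis section it occurs only in the title of a cited reference. On both points of conflict, the rest of the protocol agrees with the measures section.

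**Step 2. Illustration of size, carers only**

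Let d0, d6 and d12 be the differences between arms in mean utility at 0, 6 and 12 months. Assume a trapezoidal area under the curve, with time in years:

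- QALY gain over 0 to 6 months = 0.5 × (d0 + d6)/2
- QALY gain over 0 to 12 months = 0.5 × (d0 + d6)/2 + 0.5 × (d6 + d12)/2

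Baseline is collected before randomisation, so set d0 = 0. With d the largest difference:

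| Assumed profile | d0, d6, d12 | 0 to 6 months | 0 to 12 months | Share captured |
|---|---|---|---|---|
| Gain reached by 6 months and held | 0, d, d | 0.25d | 0.25d + 0.50d = 0.75d | 33% |
| Linear gain to 12 months | 0, 0.5d, d | 0.125d | 0.125d + 0.375d = 0.50d | 25% |
| Gain at 6 months, lost by 12 | 0, d, 0 | 0.25d | 0.25d + 0.25d = 0.50d | 50% |
| Gain only after 6 months | 0, 0, d | 0 | 0 + 0.25d = 0.25d | 0% |

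With d0 = 0 the share simplifies to d6/(2 × d6 + d12). It therefore cannot exceed one half while d6 and d12 are both non-negative. If the difference reversed sign after month 6, the share could be higher.

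**Step 3. From carer QALYs to the ratio**

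The denominator also counts care-recipient QALYs. Write C6 and C12 for the carer gain over 6 and 12 months, and R for the care-recipient gain. At fixed 12-month cost, the ratio is inflated by (C12 + R)/(C6 + R). With R = 0 and the first profile this is 0.75/0.25 = 3. For any positive R it is smaller. The protocol gives no value for R and states the 6-month limit for carers only, so the combined effect cannot be computed.

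**The case against.** The best defence is that this is a recoverable drafting error. The 12-month hypotheses, the listed measures, the survey schedule and the measures section all point the same way. An analyst who tried to apply the DEMQOL-Proxy algorithm would find no listed instrument to score and would go back to the measures section. The primary efficacy hypotheses are untouched, and no participant procedure changes. All of this stands, and it limits the harm. It does not remove the conflict, because no rule says which section governs, and the 6-month window, unlike the DEMQOL-Proxy sentence, can be carried out as written.

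A reader might also infer more than the documents support:

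- *That the trial does not collect DEMQOL-Proxy.* The survey form (Appendix F) is not shown. The text supports only that the instrument is not listed among the measures.
- *That care-recipient QALYs are lost.* QOL-AD-Proxy is a primary measure, is covered by the survey schedule, and has a named value set in the measures section.
- *That the analysis section itself divides 12-month costs by 6-month QALYs.* It states no cost horizon. The mismatch arises only if its QALYs are combined with the 12-month window of the measures section, which is plausible but not a literal instruction.
- *That the cost-effectiveness ratio is overstated two- or three-fold.* Such multipliers need an assumed utility profile and a carer-only denominator.

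**Conclusion.** The contradiction is real, stands in current text and affects the primary economic outcome. The analysis section is wrong as written on both points: its carer window omits the second half of a 12-month intervention, and it names an unlisted care-recipient instrument with a value set that does not fit the listed one.

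The size is not known. For carers alone, the 6-month window would capture 0 to 50% of the 12-month QALY gain in the four profiles above. That assumes no baseline difference, non-negative differences later and trapezoidal integration. The effect on the combined ratio is smaller or unknown. The more certain harm is to pre-specification: window and instrument remain open to choice once the data are in hand. The correction should be made before the economic analysis begins.

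**What to change.** Rewrite the QALY text under *Measuring the cost-effectiveness of the iSupport program* to match *Measures for cost-effectiveness*:

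1. Derive carer QALYs from SF-12 at baseline, 6 and 12 months.
2. Derive care-recipient QALYs from QOL-AD-Proxy with the value set cited in the measures section.
3. State that both are accumulated over the same 12 months as costs, and give that cost horizon in the analysis section too.
4. Check Appendix F. If DEMQOL-Proxy is not in the survey, remove the sentence and its reference. If it is there, add it to the listed measures and state which instrument gives the primary QALY.

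The cost is a text correction. The listed measures and the survey schedule already supply the data, and nothing changes in recruitment, randomisation or participant burden.

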**What impact will a participant withdrawing have on the data and how will this be responded to?**

We have assumed an attrition rate of 40% in sample size calculation. This sample size will ensure a participant withdrawing has little impact on the data and statistical power. A clear flow form about the numbers of participants' recruitment, allocation, withdraw, and analysis will be reported in the project reports and publications to foster transparency of the study.

A withdraw consent form will be used if participants wish to withdraw during the research. Participants will be informed that data collected up to the time of withdraw will be used unless they suggest otherwise.

## Results, reporting, outcomes and future plans

### Post approval monitoring and reporting

Once you have received ethics and governance authorisation for your research project, there are mandatory reporting requirements you must adhere to as per The National Statement chapter 5.5.

- Annual review – this is required annually for the life of the audit, on the anniversary of the approval date. Please use the template on our website.
- Final report – this is required to be submitted on completion of the audit. Please use the template on our website

Please refer to the Office for Research Reporting and Monitoring guidelines on our website for the mandatory reporting requirements for this research project.

Failure to submit the required reports of a breach of the NHRMC Australian Code for the Responsible Conduct of Research R17, R22, the National Statement chapter 5.5 and the terms and conditions of the ethical approval of the study. Failure to submit the required report may result in the ethics approval being withdrawn and the application closed.

#### **Please detail your plans for the return of the research results to the participants:**

The researchers will provide the participating organisations with a written summary of findings from the study. The summary will be ready for participating organisations to use in their newsletters and website. Therefore, participants in the project will be informed of the main findings of the project.

#### **What are your plans for dissemination and publication of project outcomes:**

The outcome will be published to journals. The result will be shared and disseminated through conference and inhouse education.

#### **Please detail other potential uses of the data at the end of the project:**

N/A

#### **What are your plans for sharing and/or future use of data and/or follow-up research? i.e. anticipated secondary use of data:**

N/A

**What is the project closure process?** I.e. a final report will be submitted to the HREC, where the study data and/or samples will be stored?

1. The final report will be produced and submitted to the HREC, MRFF/Dementia Collaborative and Research Centre.
2. Finding of the study will be reported to participants via email when the research project is completed.
3. The outcomes in this project will be published in the publications related to this topic.

